### 7.2 Secondary outcomes

- time in PP/day in awake PP if measured. This will vary at different sites and wards.
- cross-over rate to NIV,
- incidence and days of vasopressor and/or inotropic support,
- incidence and days of renal replacement therapy,
- days on ventilator for patients in need of mechanical support,
- number of patients receiving extracorporeal membrane oxygenation,
- in-hospital and ICU LOS,
- complications.
- the 7- and 30-day mortality.
- WHO ordinal scale (Fig 1) for clinical improvement at baseline, day 7 and 30.

*Fig 1. WHO ordinal scale for clinical improvement*

| Patient State  | Description                                      | Score |
|----------------|--------------------------------------------------|-------|
| Uninfected     | No clinical or virological evidence of infection | 0     |
| Ambulatory     | No limitations of activities                     | 1     |
|                | Limitations of activities                        | 2     |
| Hospitalized   |                                                  |       |
| Mild disease   | No oxygen therapy                                | 3     |
|                | Oxygen by prongs or mask                         | 4     |
| Severe disease | NIV or HFNC                                      | 5     |
|                | Intubation and mechanical ventilation            | 6     |

|      |                                                                              |   |
|------|------------------------------------------------------------------------------|---|
|      | Mechanical ventilation
+additional organ support
(pressors, RRT, ECMO) | 7 |
| Dead | Death                                                                        | 8 |

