## PROTOCOL SYNOPSIS

**English title:** Awake prone positioning with high flow nasal oxygen in critically ill covid-19 patients.

**Swedish title:** Buklägesbehandling med högflödesgrimma vid covid-19.

**Objectives:** Determine if a protocol for prone positioning with high flow nasal cannula or noninvasive ventilation reduces the rate of intubation in awake spontaneous breathing covid-19 patients or patients with other infectious disease with moderate to severe hypoxemic respiratory failure.

**Design:** Multicenter randomized controlled, parallel group, superiority trial.

**Population and Intervention:** 240 adults, 18 years or older with confirmed or strongly suspected infection with novel corona virus SARS-CoV-2 or other infectious disease, ongoing or planned oxygen treatment with high flow nasal cannula or noninvasive ventilation and moderate to severe respiratory failure as defined by a  $\text{PaO}_2/\text{FiO}_2$  ratio of  $\leq 20$  kPa ( $\approx 150$  mmHg) and/or a  $\text{FiO}_2$  of 0.5 required to reach an  $\text{SpO}_2$  of 94%.

Patients will be randomized 1:1 to a prone positioning protocol with a prone position target of 16 hours/day OR standard care.

**Outcomes:** Primary outcome is the rate of intubation. Secondary outcomes include time in prone position, admission to the ICU, time on mechanical ventilation, need for renal replacement therapy, the WHO ordinal scale for clinical improvement and the 7- and 30-day mortality and complication rate.

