## **2.1 Aim(s)**

The primary aim of this study is to determine the effect on prone positioning with HFNC or NIV on the intubation rate in critically ill COVID-19 patients or patients with other infectious disease with moderate to severe hypoxemic respiratory failure. The secondary aims include time/day in PP, 7- and 30-day mortality, days on ventilator, in-hospital and ICU LOS, incidence of RRT, the need for vasopressors and/or inotropic drugs, the WHO ordinal scale for clinical improvement, and adverse events during PP. In a subset of 30 patients we aim to study the acute effects on lung volume and function with EIT, PaO2/FiO2 ratios, respiratory rate, hemodynamic parameters and effect on dyspnea.

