## 7. OUTCOMES

### 7.1 Primary Outcome

The primary outcome is the rate of intubation.

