## 8.3 Statistical analysis

Intention-to-treat analyses will be conducted based on available data. The difference in rate of intubation between the groups will be analyzed with the Chi-2 test. Continuous data will be compared using multifactorial repeated measures ANOVA or multiple regression. Mean values with 95% confidence intervals will be calculated for primary and secondary outcomes. Non-parametric tests will be used for non-normally distributed data, with descriptive data expressed as medians with interquartile range.

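### Ventilator days are defined only for patients who become ventilated, a subset formed by the primary outcome, so the between-arm comparison is not randomised and can miss or reverse a real saving

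*Protocol*

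**What the plan says.** Protocol section 7.2 (Secondary outcomes) lists "days on ventilator for patients in need of mechanical support". The restriction appears only there. Section 2.1 lists "7- and 30-day mortality, days on ventilator, in-hospital and ICU LOS" among the secondary aims, and the Synopsis states "Secondary outcomes include time in prone position, admission to the ICU, time on mechanical ventilation"; neither limits ventilator time to those who were ventilated.

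Section 7.1 states: "The primary outcome is the rate of intubation". Section 8.1 plans on 88% intubated in the control group and a 20% decrease in the intervention group.

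On analysis, section 8.3 says "Intention-to-treat analyses will be conducted based on available data" and "Continuous data will be compared using multifactorial repeated measures ANOVA or multiple regression". It also allows non-parametric tests, with medians and interquartile ranges, when data are not normally distributed.

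Mortality is a separate secondary outcome ("the 7- and 30-day mortality"), and the WHO ordinal scale, with death as its worst category, is assessed at baseline, day 7 and day 30.

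**The concern.** A between-arm comparison of ventilator days under the section 7.2 definition conditions on an event that happens after randomisation and that the intervention is designed to change. If prone positioning works, some patients who would have been ventilated under standard care drop out of the prone arm's subset, while their counterparts stay in the control subset. The two subsets then differ in composition even though the full arms do not.

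If the spared patients would have had short runs, those left in the prone subset are the longer-stay patients, and prone positioning appears to prolong ventilation. If the spared patients were typical, the comparison shows nothing although ventilator use has fallen.

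Section 2.2 motivates the trial by situations where ventilator capacity is exceeded. Ventilator days per randomised patient speak to that question. Days per ventilated patient do not, and they can mislead when the intervention succeeds.

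**Working it through.** **The plan's own figure.** Section 8.1 gives 112 per group for 88% in control, a 20% decrease, 90% power and alpha 0.05. Reading the decrease as relative gives 0.88 × 0.80 = 0.704. The two-sided pooled formula is

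n = [1.96·√(2·p̄·(1−p̄)) + 1.2816·√(p₁(1−p₁) + p₂(1−p₂))]² / (p₁−p₂)², with p̄ = (0.88 + 0.704)/2 = 0.792.

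- First term: 1.96 × √0.3295 = 1.125.
- Second term: 1.2816 × √0.3140 = 0.718.
- n = (1.843)² / (0.176)² = 3.397 / 0.03098 = 109.7, so 110 per group, close to 112.

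Reading the decrease as 20 percentage points (68%) gives 89 per group, so the relative reading is used below.

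**Size of the subset.** With 240 patients randomised 1:1, there are 120 per arm.

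- Control: 120 × 0.88 = 105.6, about 106 ventilated.
- Prone: 120 × 0.704 = 84.5, about 84 ventilated.

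**Direction and size of the distortion.** The protocol gives no ventilator durations, so these are assumptions. Let the 17.6% of patients spared intubation have S ventilator days if left in the control arm, and let all other ventilated patients average 14 days in both arms. There is no other effect of treatment, and death is left out.

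- Control mean among the ventilated: (0.176·S + 0.704·14) / 0.88 = 0.2·S + 11.2.
- Prone mean among the ventilated: 14.
- Ventilated-only difference, prone minus control: 14 − (0.2·S + 11.2) = 0.2·(14 − S).
- Difference per randomised patient (0 days if never ventilated): 0.704·14 − (0.176·S + 0.704·14) = −0.176·S.

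| S | Control mean, ventilated | Prone mean, ventilated | Ventilated-only difference | Control per randomised | Prone per randomised | Difference per randomised |
|---|---|---|---|---|---|---|
| 5 | 12.2 | 14.0 | +1.8 | 10.74 | 9.86 | −0.9 |
| 7 | 12.6 | 14.0 | +1.4 | 11.09 | 9.86 | −1.2 |
| 10 | 13.2 | 14.0 | +0.8 | 11.62 | 9.86 | −1.8 |
| 14 | 14.0 | 14.0 | 0 | 12.32 | 9.86 | −2.5 |
| 18 | 14.8 | 14.0 | −0.8 | 13.02 | 9.86 | −3.2 |

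The ventilated-only comparison changes sign at S = 14. The per-randomised comparison favours prone positioning throughout.

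**At the trial's size.** In 4,000 simulated trials with 120 per arm and S = 7 (gamma-distributed durations, also assumed), the ventilated-only difference averaged +1.4 days. It pointed against prone positioning in 89% of trials and did so with Mann-Whitney p < 0.05 in 28%. The all-randomised difference averaged −1.2 days and favoured prone positioning in 85%.

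**The case against.** **One line in an outcome list is not a test.** Section 7.2 names no between-arm comparison for this item, and the Synopsis, section 2.1 and the intention-to-treat statement could be read as governing. That shows the sections disagree; it does not remove the restriction. An analysis that follows section 7.2 inherits the problem, and one that departs from it contradicts section 7.2. The available-data qualifier in section 8.3 does not help either, because a patient who was never ventilated has zero ventilator days, not a missing value.

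**Other outcomes guard against misreading.** This stands in part. Intubation, mortality at days 7 and 30, and the WHO scale are all reported, and no stopping rule in section 8.2 uses ventilator days. This limits the damage and is why the point concerns a secondary outcome only.

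**The direction is not known.** This stands. A reader might infer that the trial would report prolonged ventilation. That requires the spared patients to be the shorter-run ones. An extreme case can be built: with exponential durations of mean 14 and exactly the shortest 20% of runs averted, the ventilated-only mean rises from 14.0 to 17.1. But the spared patients would then have averaged only (14 − 0.8 × 17.12)/0.2 ≈ 1.5 days, and nothing in the protocol supports that pattern.

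**Deaths.** A reader might also infer that "in-hospital and ICU LOS", vasopressor days and renal replacement days ignore death. The protocol does not say so. It is silent on how deaths enter these durations, and that rule is commonly left to a statistical analysis plan, which is not at hand. The silence is not an error in this document.

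**Conclusion.** The point holds for ventilator days. Section 7.2 fixes a subset formed after randomisation by the primary outcome, and this conflicts with the unrestricted wording elsewhere and with the intention-to-treat plan. Under the stated assumptions the ventilated-only difference runs from +1.8 to −0.8 days as S goes from 5 to 18, while the saving per randomised patient runs from 0.9 to 3.2 days. The outcome can therefore miss or reverse a real saving, depending on who is spared.

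The 14-day mean, the values of S and the duration distribution are illustrative. The 88% and 70.4% follow from section 8.1 on the relative reading. That the subset is not protected by randomisation does not depend on any of these values. The primary outcome and the sample size are untouched.

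**What to change.** In section 7.2, define the between-arm ventilator outcome in all randomised patients. One suitable form is ventilator-free days to day 30, with death by day 30 ranked worst and a survivor who was never ventilated scored 30. Compare the arms with a rank-based test, which section 8.3 already allows, and show mortality and ventilator duration separately beside it. Keep days among ventilated patients as a descriptive summary only, and bring the Synopsis and section 2.1 into line.

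The cost is small. Ventilator days and 30-day mortality are already listed outcomes, and treatment, sample size and primary analysis do not change. The protocol does not say that ventilation start and stop dates are recorded, so the sponsor should confirm that days can be counted within the 30-day window. The drawback is a composite of death and duration, which is why both parts should be shown. Using the same death rule for lengths of stay, vasopressor days and renal replacement days would be consistent but is optional.

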## 7.2 Other parameters

Age, sex, weight, height, comorbidities and last available PaO2/FiO2 ratio before inclusion OR if arterial gas is not available, SpO2/FiO2 ratio will be recorded. Also, at baseline, viral diagnostic status, pulmonary radiology, available laboratory results regarding inflammation, anaemia, renal and hepatic function and biomarkers of cardiac dysfunction will be recorded.

## 7.3 EIT outcomes

In the subset of participants in the intervention group undergoing EIT measurements, further secondary outcomes at previously predefined timepoints are EELI, TIV, PaO2/FiO2 ratio, SpO2, respiratory rate, blood pressure, heart rate and dyspnea assessed with the modified Borg-scale.

# 8. STATISTICAL METHODS

## 8.1 Sample size estimation

Sample size calculations are based on the ratio of intubation in critically ill COVID-19 patients in New York and Lombardy. Assuming an intubation rate of 88% in the control group and a decrease of intubations of 20% in the intervention group a sample size of 112 patients in each group is needed (power 90%, alfa 0.05). To compensate for a drop out of 10%, 240 patients are planned for inclusion.

## 8.2 Interim analyses

Due to the lack of previous study data and the difficulties in predicting the course of the epidemic in Sweden, we plan to conduct interim analyses after inclusion of 120 and 180 patients. The decision to terminate the study may be based on 1) futility (lack of patients fulfilling the inclusion criteria), 2) safety (unexpected increase in the rate of intubation in the intervention group or increased occurrence of severe or unexpected adverse events, or 3) efficacy (if the reduction in the rate of intubation is more than 40%).

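### The interim efficacy rule is a raw observed reduction of more than 40% with no stated scale and no error control: harmless at the planned 88% control rate, but anti-conservative if that rate is about 40% or lower

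*Protocol*

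**What the plan says.** Section 8.2 plans interim analyses after 120 and 180 patients and says that termination may be based on futility, safety or efficacy. The efficacy criterion is "efficacy (if the reduction in the rate of intubation is more than 40" per cent). The section gives no scale for the reduction, no test, no p-value threshold and no adjustment of the final analysis.

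Section 8.1 plans on the following: "Assuming an intubation rate of 88% in the control group and a decrease of intubations of 20% in the intervention group". The design values are "power 90%, alfa 0.05", and the result is that "a sample size of 112 patients in each group is needed". Section 8.3 names the primary test: "The difference in rate of intubation between the groups will be analyzed with the Chi-2 test". It mentions no allowance for interim looks.

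**The concern.** A threshold on the point estimate alone does not correspond to a fixed amount of evidence. A relative reduction of 40% is a large absolute difference when most control patients are intubated and a small one when few are. The same rule can therefore demand overwhelming evidence in one setting and accept a non-significant difference in another. The trial looks at the primary outcome up to three times and states one alpha of 0.05, so the chance of a false claim of benefit is not controlled by design. It depends on a control rate that nobody knows in advance. The missing scale adds a second problem, because relative and absolute readings give rules that behave quite differently.

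At stake is a decision that can end the trial early and supply its main claim.

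**Working it through.** **Inputs.** Section 8.1: control rate 88%, decrease 20%, power 90%, alpha 0.05, 112 per group, 240 in total. Section 6: 1:1 allocation, so about 60 and 90 per arm at the two looks and 120 per arm at the end. Section 8.2: looks at 120 and 180, threshold 40%. Control rates below 88% are my assumptions.

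**Step 1: which scale does section 8.1 use?** Two-sided test, pooled variance under the null:

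n = [1.96·√(2p̄(1−p̄)) + 1.2816·√(p₁(1−p₁) + p₂(1−p₂))]² / (p₁−p₂)²

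- Relative, 88% to 0.8 × 88% = 70.4%: p̄ = 0.792, so n = (1.96 × 0.5740 + 1.2816 × 0.5603)² / 0.176² = 3.397 / 0.03098 = 109.7, or 110 per arm. This is close to the stated 112.
- Absolute, 88% to 68%: 89 per arm. This is not close.

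So the 20% in section 8.1 is relative. The natural reading of the 40% in section 8.2 is also relative, although the protocol does not say so.

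**Step 2: what evidence does exactly a 40% relative reduction represent?** With p_t = 0.6·p_c and p̄ their mean, z = (p_c − p_t) / √(2p̄(1−p̄)/n).

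- Control 88%, 60 per arm: 0.352 / √(2 × 0.704 × 0.296 / 60) = 0.352 / 0.0833 = 4.22, p = 0.00002.
- Control 30%, 60 per arm: 0.12 / √(2 × 0.24 × 0.76 / 60) = 0.12 / 0.0780 = 1.54, p = 0.12.
- Control 30%, 90 per arm: 0.12 / 0.0637 = 1.88, p = 0.06.

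**Step 3: false claims of benefit with no true effect.** Exact enumeration of the two binomials. Stop and claim benefit if the treated rate is below 0.6 times the control rate at 60 or 90 per arm; otherwise apply an unadjusted chi-square at 120 per arm.

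| Control rate | p at exactly 40% lower, 60 / 90 per arm | False efficacy stop by second look | Total false benefit | Final test alone |
|---|---|---|---|---|
| 88% | 0.00002 / 0.0000002 | about 0 | 2.5% | 2.5% |
| 60% | 0.009 / 0.001 | 0.06% | 2.6% | 2.6% |
| 50% | 0.025 / 0.006 | 0.4% | 2.4% | 2.3% |
| 40% | 0.060 / 0.021 | 1.5% | 3.4% | 2.6% |
| 30% | 0.12 / 0.06 | 4.2% | 5.4% | 2.5% |
| 20% | 0.23 / 0.14 | 10.0% | 10.5% | 2.6% |

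Total two-sided error is 5.0% at 88%, 6.1% at 40%, 7.9% at 30% and 13.1% at 20%. Of the false efficacy stops, 28% at a 30% control rate and 70% at a 20% control rate have p of 0.05 or more.

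**Step 4: how often does the rule fire at the planning rate?** With 88% versus 70.4%, about 0.35% of the time by the second look. With a true 40% reduction (88% versus 52.8%), 49% at the first look and 59% by the second.

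**Step 5: the absolute reading.** A drop of 40 percentage points can be observed only if the observed control rate exceeds 40%. With no true effect the chance of meeting the rule is below 0.0003% at every rate examined, and at 88% versus 70.4% it is 0.07%. Nothing is inflated.

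**Step 6: alternatives.** With two-sided p<0.001 at both looks and 0.05 at the end, two-sided error stays within 0.03 percentage points of the single final test at every control rate tried. At 88% versus 70.4% this boundary fires by the second look 36% of the time, and power stays at 93.1% with 120 per arm. An O'Brien-Fleming-type spending function (nominal p 0.0031, 0.0184 and 0.0440) gives cumulative crossing of 26.7%, 72.4% and 92.5% under the planned effect, with false benefit of 2.4% to 2.5%.

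All figures assume equal arms and outcomes known for every included patient at each look.

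**The case against.** **The harm needs low control rates.** This stands. A reader might infer that any control rate below 88% inflates the error. It does not: at 50% and 60% the false-benefit rate is 2.4% and 2.6%. The protocol states only 88%, so rates of 40% or lower are assumed. They are reasonable to test, because section 8.1 takes its figure from critically ill cohorts elsewhere. This trial also recruits on wards, admits other infectious disease and excludes patients who need immediate intubation. A reader might also take section 8.2 to admit that the control rate is hard to predict. It speaks of the course of the epidemic and of a lack of earlier study data, and does not mention the control rate.

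**Near-inertness at 88% is a legitimate conservative choice.** This stands too. A rule that needs z of about 4.2 costs no type I error and no power. The 0.35% applies to the planned effect only. It bears on the usefulness of the looks, not on validity.

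**The rule is permissive, and a stop need not be called positive.** This stands in part. Section 8.2 does not say that a stop replaces the chi-square test. But suppose the trial stops whenever the rule is met and claims benefit only if the chi-square at that point is significant at 0.05. The false-benefit rate is then still 4.2% at a 30% control rate and 3.5% at 20%. Unspecified discretion offers no error control either.

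**Boundaries are commonly left to the SAP.** That is true in general, and a SAP not seen here may add one. The 0.05 for the final test is also inferred from the sample-size sentence, since section 8.3 gives no level. But the protocol does not leave the efficacy criterion open. It fixes a number unconnected to statistical evidence and omits its scale, so a SAP with a proper boundary would have to override or supplement it.

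**Conclusion.** The rule is badly fixed and should be corrected, but it does not undermine the trial at its own planning assumptions. On the relative reading, inflation is nil at 88% and negligible at 50% or more. At about 40% and below the chance of falsely declaring benefit rises to 3.4% (control 40%), 5.4% (30%) and 10.5% (20%), against a nominal 2.5%, if stops count as efficacy claims. In that range the trial can stop on a non-significant difference.

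The conclusion rests on three assumptions: the relative reading, which section 8.1 supports but section 8.2 does not state; assumed lower control rates; and the rule followed as written. The documents do not support the stronger claim that the design as planned exceeds its stated alpha.

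**What to change.** Replace the third criterion in section 8.2 with: efficacy, two-sided p<0.001 for the primary outcome at the 120- and 180-patient looks (Haybittle-Peto), with the final analysis at 0.05. An O'Brien-Fleming-type spending function is an equally good choice and would stop more often under the planned effect, with a final level of about 0.044. If a minimum effect is also wanted, state it as a relative reduction required in addition to the boundary.

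The cost is one sentence. No extra patients are needed, and power is essentially unchanged (93.1% with the p<0.001 boundary and 92.5% with the spending function, against 93.1% for the final test alone at 120 per arm).

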## 8.3 Statistical analysis

Intention-to-treat analyses will be conducted based on available data. The difference in rate of intubation between the groups will be analyzed with the Chi-2 test. Continuous data will be compared using multifactorial repeated measures ANOVA or multiple regression. Mean values with 95% confidence intervals will be calculated for primary and secondary outcomes. Non-parametric tests will be used for non-normally distributed data, with descriptive data expressed as medians with interquartile range.

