## 6. RANDOMIZATION AND BLINDING

Patients will be randomized 1:1 in blocks of four at each center. The randomization outcome is obtained via a web-based service provided by the coordinating center. The patient, the treating physician/-s and other care providers will not be blinded to the study allocation. Assessors will be blinded during analysis.

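### Randomisation is blocked within centre, but the primary chi-square ignores centre and the recorded baseline oxygenation: a valid, mildly conservative test that gives up a little power

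*Protocol*

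**What the plan says.** - Protocol section 6: "Patients will be randomized 1:1 in blocks of four at each center". Centre is therefore a stratification factor.
- Protocol section 7.1: "The primary outcome is the rate of intubation", a binary outcome for each patient.
- Protocol section 8.3: "The difference in rate of intubation between the groups will be analyzed with the Chi-2 test". No centre term or covariate is named. The only regression in the section is reserved for another data type: "Continuous data will be compared using multifactorial repeated measures ANOVA or multiple regression".
- Protocol section 8.3 also promises an interval: "Mean values with 95% confidence intervals will be calculated for primary and secondary outcomes".
- Protocol section 7.2 (Other parameters) lists the baseline data, starting "Age, sex, weight, height, comorbidities and last available" PaO2/FiO2, with SpO2/FiO2 as the substitute where there is no blood gas. Section 8.3 does not use either ratio.
- Protocol section 8.1 sizes the trial as an unadjusted comparison of two proportions: "Assuming an intubation rate of 88% in the control group and a decrease of intubations of 20% in the intervention group", with 112 per group, 90% power and alpha 0.05.

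**The concern.** Blocking within centre keeps the arms balanced inside each centre, so differences in intubation rate between centres largely drop out of the arm comparison. The pooled chi-square still counts those differences as noise. Its standard error is then too large, its p-value slightly too big and the matching interval too wide.

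Differences between centres are plausible here. Section 5.3 leaves the decision to intubate to the treating intensivist and other care to local guidelines, and section 5.1.2 leaves proning of control patients to the treating physician.

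Baseline oxygenation raises a separate and simpler issue. It was not a stratification factor, so leaving it out does not distort the standard error. It only forgoes precision that a prognostic covariate would give. At stake is power that the design and the data collection already provide.

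**Working it through.** **1. The plan's own figure.** Inputs from section 8.1: control rate 0.88; a 20% decrease read as relative gives 0.88 × 0.80 = 0.704; two-sided alpha 0.05; power 90%. The mean rate is 0.792.

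n per group = [1.960 × √(2 × 0.792 × 0.208) + 1.282 × √(0.88 × 0.12 + 0.704 × 0.296)]² / 0.176²
= (1.125 + 0.718)² / 0.03098 ≈ 110.

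The plan states 112, so the figure reproduces. Power at 112 per group: Φ[(√112 × 0.176 − 1.125) / 0.560] = Φ(1.316) = 90.6%. At all 240 patients (120 per group): Φ(1.433) = 92.4%. The unadjusted test is consistent with the stated power.

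**2. Assumptions not in the documents.** 3, 5 or 10 equal centres (six centres of 40 for the 60% versus 42% case); N = 240 balanced within centre; SD of the centre log-odds from 0 to 1.0; overall rates held at the stated values. An SD of 1.0 is large. At 88% the log-odds is 1.99, so ±2 SD spans centre rates of about 50% to 98%.

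**3. Simulated power, chi-square against Cochran-Mantel-Haenszel (CMH) by centre.**

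| Rates | Centre SD | Chi-square | CMH | Gain (points) |
|---|---|---|---|---|
| 88% v 70.4% | 0.3 | 93.1–93.6% | 93.1–93.6% | about 0 |
| 88% v 70.4% | 0.5 | 93.3–93.6% | 93.6–93.9% | 0.3 |
| 88% v 70.4% | 1.0 | 94.2–94.3% | 95.5–95.7% | 1.3–1.5 |
| 40% v 22% | 0.5 | 86.5–86.7% | 87.7–87.9% | 1.2–1.3 |
| 40% v 22% | 1.0 | 87.7–87.8% | 91.0–91.1% | 3.3–3.4 |
| 60% v 42% | 0.8–1.0 | 81.2–81.9% | 84.6–86.7% | about 3.5–5 |

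With no centre differences the two tests agree to within about 0.3 points.

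**4. Adding baseline oxygenation.** With an assumed 0.7 to 1.0 log-odds per SD, logistic regression on centre and the covariate raises power at 88% versus 70.4% from about 93–94% to 95–97%, a gain of 2 to 3.5 points. At 40% versus 22% the gain is about 2.5 to 6 points. These runs used 2,500 trials each, so one power figure near 94% carries a Monte Carlo SE of √(0.94 × 0.06 / 2500) ≈ 0.5 points.

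**5. Validity of the unadjusted test.** Over the fixed-centre scenarios, which took 88% or 40% as the control rate, the mean unadjusted SE is 0.99 to 1.11 times the true SE, and its 95% interval covers 94.4% to 96.8%. Type I error is 3.1% to 5.4% for chi-square and 4.7% to 5.2% for CMH. The SE ratios explain this: an SE 11% too large gives 2 × [1 − Φ(1.96 × 1.11)] = 3.0%, and one 4% too large, as at 88% with SD 1.0, gives 4.2%. The low values near 3% therefore belong to middling rates with strongly differing centres, not to the planning case. The stratified interval is 0 to 10% narrower.

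**The case against.** The best defence is that test and sample size match. Section 8.1 is an unadjusted two-proportion calculation, section 8.3 applies the corresponding test, and the 90% power is met. The number of centres, the spread between them and the lower-rate scenarios are all assumed. At a centre SD of 0.3 to 0.5 the loss at the planning rates is 0 to 0.3 points. Covariate sets and effect measures are also commonly left to an analysis plan, which is not at hand. This stands as a limit on size. It does not remove the point, because the protocol does name the primary test, and that test leaves out the factor used in randomisation.

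Three stronger readings are tempting and not supported:

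- **That the error bars are wrong in a harmful direction.** They are right if centres do not differ and too wide if they do. Type I error does not materially exceed 5%.
- **That power falls below 90%.** Adding centre effects on the log-odds scale without holding the overall rates gives about 89% to 91% for chi-square. The realised rates are then about 84–86% versus 67–68%, which are not the planned ones.
- **That the plan yields no effect size.** Section 8.3 speaks of a difference in rates and promises 95% intervals, and the mean of a 0/1 outcome is a proportion. The wording is loose, but an analysis plan would settle it.

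**Conclusion.** The point holds as a modest loss of efficiency. The primary test is valid and, where centres differ, mildly conservative. At the planned 88% versus 70.4%, ignoring centre costs about 0 to 1.5 points of power, and ignoring a prognostic baseline oxygenation value as well brings this to about 2 to 3.5. If intubation is less common than planned, the cost of ignoring centre is larger: up to about 5 points at 60% versus 42%. All of these sizes rest on the assumed centre numbers, spreads and prognostic strength, and the loss from centre vanishes if centres are alike. Nothing here undercuts the stated 90% power or would make a positive result unsafe. The change is worth making because it gains where centres differ and costs almost nothing where they do not.

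**What to change.** In section 8.3, replace the plain chi-square as primary analysis with one of:

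- a CMH test stratified by centre, with the matching stratified risk difference and 95% CI; or
- a logistic model with arm, centre and baseline oxygenation, reported as a regression-standardised risk difference with 95% CI.

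Set two rules before the data are examined by arm:

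- **Pooling of small centres.** At the planned rates only about 0.12 × 120 + 0.296 × 120 ≈ 50 patients would not be intubated, or about five per centre with ten centres, so some centres may have none.
- **Combining the two ratios.** PaO2/FiO2 and SpO2/FiO2 are on different scales and should not be entered as one variable. Separate terms with an indicator for which was measured would do.

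Keep the plain chi-square as a sensitivity analysis. The cost is wording plus these two rules; centre and both ratios are already recorded, and the sample size need not change.
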